### Plans to give access to the full protocol, participant level-data and statistical code {31c}

The full study protocol, statistical code, and dataset will be available from the corresponding author upon request.

## Oversight and monitoring

### Composition of the coordinating center and trial steering committee {5d}

The steering committee will meet every 3rd month to evaluate the inclusion and the progression of the study.

### Composition of the data monitoring committee, its role and reporting structure {21a}

The trial is expected to be a low-risk intervention and therefore a data monitoring committee has not been considered necessary.

### Adverse event reporting and harms {22}

The symptoms of treatment-resistant patients will often fluctuate and can lead to severe events like violence or suicidal behavior. In case of worsening of psychotic symptoms or sleep disturbances, the treating psychologist will discuss with the patient whether the intervention should be terminated. The final decision to terminate is made by the psychologist.

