### Criteria for discontinuing or modifying allocated interventions {11b}

The psychotherapeutic intervention in both groups will be adjusted continuously for each trial participant given the individual nature. In the unlikely event that either intervention should result in a worsening of the psychotic symptoms, both the participant and the clinician providing the intervention can decide to discontinue the intervention, ideally in a way resembling shared decision-making.

Furthermore, 2 untimely cancelations or failures to appear in a row are considered non-compliance with the treatment, and the participant is excluded from the study.

Lastly, a change in a participant’s psychopathology which results in either substantial changes in antipsychotic medication or admittance lasting ≥ 7 days will result in exclusion from the study as per the exclusion criteria.

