A core characteristic of clinical insomnia is that the affected person engages in compensatory strategies, for example, extension of total time spent in bed, withdrawal from occupational or private commitments, and/or inappropriate use of substances (illicit or otherwise) to either stay awake or fall asleep. In the CBT-I intervention, we employ SRT by restricting participants’ sleep opportunity (the time they are allowed to be in bed) for a period. We wish to inhibit the compensatory strategies that participants engage in, which perpetuate their sleep disturbances. However, we need to be careful in applying this therapeutic tool, since sleep deprivation is a factor in triggering and perpetuating psychosis. By using sleep restriction, we are, in a sense, lowering participants’ psychosis threshold, which is potentially problematic if it is not done in a controlled manner. To mitigate this risk, we have decided to not restrict below 5 h to prevent the worst sleep deprivation [42]. Furthermore, participants are seen by the therapist weekly, where they systematically assess the effect of SRT and any potential recurrence of psychotic symptoms. This enables the therapist and participant to collaborate on how to manage psychotic symptoms and when to potentially terminate the intervention. By taking these preventative steps, we want to ameliorate the potential adverse outcomes of CBT-I.

It can be challenging to adhere to a psychotherapeutic intervention, especially for people who meet the criteria for severe psychiatric disorders. Efficient psychotherapy requires sustained commitment, concentration, and a willingness to restructure thoughts and behaviors. Non-adherence is a potential pitfall, which makes the initial motivational work and sustained focus on maintaining motivation an important factor for success. During the initial contact, we will thoroughly explain the rationale and mechanisms of the interventions to enhance transparency and participants’ understanding. We have allocated a significant amount of time in the intervention manuals for motivational work, which we will tailor for each participant based on their specific situation. Throughout treatment, the therapist will routinely monitor each participant’s progress and provide support to keep motivation high. Furthermore, the procedures laid out in the intervention manuals require that time is allocated to refresh the rationale and mechanisms throughout the sessions.

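### Exclusion for deterioration, a four-session analysis population and LOCF could mask a harm concentrated in the CBT-I arm, and no by-arm reporting of discrete events is stated

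*Protocol article*

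**What the plan says.** All references are to the protocol article.

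- **Adverse event reporting and harms {22}.** Fluctuating symptoms in this population "can lead to severe events like violence or suicidal behavior". The stated response is: "In case of worsening of psychotic symptoms or sleep disturbances, the treating psychologist will discuss with the patient whether the intervention should be terminated". It adds: "The final decision to terminate is made by the psychologist".
- **Discussion.** The authors acknowledge that "sleep deprivation is a factor in triggering and perpetuating psychosis", and say of sleep restriction that "we are, in a sense, lowering participants’ psychosis threshold". They regard this as a problem if it is done without control. They give two safeguards: no restriction below 5 h, and weekly assessment by the therapist.
- **Data monitoring committee {21a}.** "The trial is expected to be a low-risk intervention and therefore a data monitoring committee has not been considered necessary".
- **Discontinuing or modifying interventions {11b}.** A change in psychopathology that leads to substantial antipsychotic changes or an admission of 7 days or more "will result in exclusion from the study as per the exclusion criteria". Concomitant care {11d} repeats the rule. On stopping therapy for worsening psychotic symptoms, {11b} says that "both the participant and the clinician providing the intervention can decide to discontinue the intervention".
- **Non-adherence and missing data {20c}.** The analysis population is patients who completed four therapy sessions. LOCF is the imputation method for the intention-to-treat analyses.
- **Outcomes {12}, statistical methods {20a} and blinding {17a}.** ISI and PANSS (total and subscales) are compared between arms at 12 and 24 weeks, and external raters score PANSS from video. Neither {12} nor {20a} lists a harms outcome or analysis.

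**The concern.** The document foresees a specific harm that belongs to one arm: sleep restriction might provoke psychotic worsening. The natural evidence on whether it does is what happens to patients who deteriorate. Three stated rules act on exactly those patients: exclusion after an antipsychotic change or admission, the four-session requirement, and LOCF. If the foreseen harm occurs, these rules would act more often in the CBT-I arm, and the two arms would look more alike than they were.

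At stake is both the safety picture and the PANSS comparison. A positive result would be used to recommend CBT-I as easy to implement in complex patients (abstract and Discussion), and readers will want to know whether psychosis worsened in some of them.

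**Working it through.** The plan states no figure for harms, so the main check sets its rules side by side. A short calculation follows.

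**1. Follow a CBT-I patient who deteriorates.** Outcomes are measured only at baseline, 12 weeks and 24 weeks ({12}).

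- *Therapy stopped for worsening after session 2 or 3.* Session 2 is treatment initiation, so I take sleep restriction to start about then. The patient has not completed four sessions and is outside the analysis population ({20c}).
- *Admission of 7 days or more, or a substantial antipsychotic change, before week 12.* The patient is excluded from the study ({11b}, {11d}). If left out of the analysis, the deterioration is not seen. If kept by LOCF, the only value available is baseline, so the imputed change is baseline − baseline = 0.
- *The same trigger between weeks 12 and 24.* The week-12 value, from before the event, stands in for week 24.

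The article does not say how the four-session population and the intention-to-treat set relate. On either reading, the deterioration does not enter the comparison.

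**2. Effect on an arm mean.** The arm has 60/2 = 30 patients. Let k of them worsen by d on PANSS and be removed, and let the other 30 − k change by m on average. The true mean change is [(30 − k)m + kd]/30.

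- With LOCF at baseline, the reported mean is (30 − k)m/30, so worsening is understated by kd/30.
- With removal, the reported mean is m, so worsening is understated by k(d − m)/30.

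Both are zero only if k = 0, or if the removed patients fared no worse than the value assigned to them. The article gives no basis for k or d, so I put no number on this.

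**3. Is there another route by which the events would be seen?** Admissions, antipsychotic changes, stopped therapy, and suicidal or violent events appear in {11b}, {11d} and {22} as triggers or anticipated events. None appears in {12} or {20a} as something reported by arm. Routine notes would not be comparable either: control patients log psychiatric symptoms and CBT-I patients log sleep ({11a}, {11c}), and different psychologists deliver the two arms.

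**4. What complete recording could show.** With zero events in n patients, the exact one-sided 95% upper bound is 1 − 0.05^(1/n).

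- n = 30 per arm: 1 − 0.05^(1/30) = 9.5%.
- n = 24, the follow-up target in Sample size {14}: 1 − 0.05^(1/24) = 11.7%.
- Upper limits of two-sided 95% intervals, 1 − 0.025^(1/n): 11.6% and 14.2%.

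For assumed true risks of 20% against 5%, Fisher's exact test with 30 per arm has about 24% power; for 30% against 10%, about 37%. The comparison can only be descriptive.

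**5. Who stops therapy.** {11b} gives the decision to participant and clinician and names psychotic worsening only. {22} gives the final decision to the psychologist and names psychotic or sleep worsening. A count of therapy stopped for worsening has no single definition until these agree.

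**The case against.** The strongest reply is that this is a condensed article. A full protocol exists, and adverse event definitions, forms and safety tables commonly sit there. That stands: the brevity of {22} does not show that nothing is recorded, and a reader should not infer it. The point rests instead on rules the article does state, which would conflict with an all-randomised safety comparison wherever that comparison was described.

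Second, a reader might infer that harm is not compared by arm at all. That goes too far. The two kinds of worsening named in {22}, psychotic symptoms and sleep, are measured by PANSS and ISI in both arms, with external PANSS rating. A general worsening under CBT-I among patients who stay would be visible. What would be missed is worsening in those who leave, and discrete events.

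Third, the risk statement is hedged and comes with two safeguards. That also stands, but the safeguards manage individual risk and do not produce data by arm.

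Fourth, the exclusion triggers apply equally to both arms. True, but equal rules remove unequal numbers if the harm is unequal, which is the case of interest.

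**Conclusion.** The point holds in a bounded form. Followed as written, the exclusion, four-session and LOCF rules can take deteriorating patients out of the by-arm PANSS and ISI comparison or score them at a value from before they deteriorated. The article states no by-arm reporting of discrete events that would compensate. A harm concentrated in the CBT-I arm could therefore be masked. It is worth correcting, and its size cannot be derived from the document.

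This rests on two assumptions: that exclusion from the study ends outcome collection, which is the plain reading, and that no unshown document overrides the stated rules.

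Two stronger readings are not supported. One is that the trial plans to declare CBT-I low-risk: {21a} states a prior expectation to explain the absence of a committee, and with the safeguards in the Discussion it need not be reworded. The other is that excluded patients' events would go unreported or be booked as ordinary attrition: no section says how exclusions and their reasons will be classified.

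**What to change.** 1. Keep every randomised patient in follow-up to week 24 for outcomes and events, including those whose therapy stops or who meet an exclusion rule. This concerns data collection only and leaves the rules for stopping therapy as they are.
2. Treat the {11b}/{11d} triggers as reported harm events and not as removals from the data.
3. Report by arm, over all randomised patients, counts with 95% intervals for: admission, substantial antipsychotic change, therapy stopped for worsening, and suicidal or violent events. Record them in the same way in both arms and present them descriptively, without a test.
4. Reconcile {11b} and {22} on who decides to stop the intervention and for which kind of worsening. Which rule is right is for the investigators.

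The cost is a short amendment, one extra table, and staff time to record events for patients who have left therapy. The intervals will be wide, as the 9.5% bound shows. The timing is favourable: Trial status reports 5 patients included by 12 January 2026, so 60 − 5 = 55 of the planned 60 would enrol under the amended rules if it is made soon.

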### Frequency and plans for auditing trial conduct {23}

Not applicable, no auditing trial conduct planned.

### Plans for communicating important protocol amendments to relevant parties (e.g., trial participants, ethical committees) {25}

Important changes to the protocol will be written in amendments and in information material which will be approved by the National Ethical Committee. 

### Dissemination plans {31a}

The results of the project will be published in internationally recognized peer-reviewed journals. The project will be a Ph.D. project, and the primary author of the articles will be the Ph.D. student, [name]. Other authorships will be allocated according to the principles of the International Committee of Medical Journal Editors (ICJME). Positive, negative, and inconclusive results will be published alike.

## Discussion

Sleep disturbances in psychiatric patients are often overlooked in clinical treatment, and with the present study, we aim at contributing to prevention, amelioration, and treatment of TRS by increasing sleep quality. TRS is a heterogenous group of patients that are heavily burdened by symptoms, suboptimal medication effect, and significant side effects. Systematically focusing on sleep to alleviate the suffering of this group is an avenue of unknown potential. If CBT-I shows positive results in TRS, it offers an easy-to-implement, cost-effective intervention.

This project involves human participants who are given one of two CBT interventions. The interventions themselves pose no real ethical issues, apart from the possible psychological discomfort associated with working on difficult subjects in therapy. The potential ethical issue of, knowingly or unknowingly, giving preferential treatment to the active treatment group is mitigated in this project by offering the active control group a CBT intervention with a specific focus on patients’ psychopathology. This is comparable in both quality and evidence base to the CBT-I intervention. This ensures that all participants in the project receive a high-quality intervention regardless of which group they are randomized into.

A core characteristic of clinical insomnia is that the affected person engages in compensatory strategies, for example, extension of total time spent in bed, withdrawal from occupational or private commitments, and/or inappropriate use of substances (illicit or otherwise) to either stay awake or fall asleep. In the CBT-I intervention, we employ SRT by restricting participants’ sleep opportunity (the time they are allowed to be in bed) for a period. We wish to inhibit the compensatory strategies that participants engage in, which perpetuate their sleep disturbances. However, we need to be careful in applying this therapeutic tool, since sleep deprivation is a factor in triggering and perpetuating psychosis. By using sleep restriction, we are, in a sense, lowering participants’ psychosis threshold, which is potentially problematic if it is not done in a controlled manner. To mitigate this risk, we have decided to not restrict below 5 h to prevent the worst sleep deprivation [42]. Furthermore, participants are seen by the therapist weekly, where they systematically assess the effect of SRT and any potential recurrence of psychotic symptoms. This enables the therapist and participant to collaborate on how to manage psychotic symptoms and when to potentially terminate the intervention. By taking these preventative steps, we want to ameliorate the potential adverse outcomes of CBT-I.

It can be challenging to adhere to a psychotherapeutic intervention, especially for people who meet the criteria for severe psychiatric disorders. Efficient psychotherapy requires sustained commitment, concentration, and a willingness to restructure thoughts and behaviors. Non-adherence is a potential pitfall, which makes the initial motivational work and sustained focus on maintaining motivation an important factor for success. During the initial contact, we will thoroughly explain the rationale and mechanisms of the interventions to enhance transparency and participants’ understanding. We have allocated a significant amount of time in the intervention manuals for motivational work, which we will tailor for each participant based on their specific situation. Throughout treatment, the therapist will routinely monitor each participant’s progress and provide support to keep motivation high. Furthermore, the procedures laid out in the intervention manuals require that time is allocated to refresh the rationale and mechanisms throughout the sessions.

## Trial status

Protocol version 1.5, 11th June 2025.

Recruitment began 28th November 2024 and will be completed approx. 31^st^ December 2026.

As per January 12, 2026, 10 patients have been screened, 5 patients have been included, and 3 patients have completed the trial.

## Data Availability

We plan to publish the final results in a peer-reviewed journal, whether they are positive, negative, or inconclusive. Furthermore, the final dataset from the study will be provided upon request.

## Abbreviations

CBT: Cognitive behavioral therapy
CBT-I: Cognitive behavioral therapy or insomnia
FAST: Functioning Assessment Short Test
GAF: Global Assessment of Functioning Scale
ISI: Insomnia Severity Index
PANSS: Positive and Negative Syndrome Scale
PSG: Polysomnography
PSP: Personal and Social Performance Scale
PSQI: Pittsburgh Sleep Quality Index
QPR: The Process of Recovery Questionnaire
SCT: Stimulus control therapy
SE: Sleep efficiency
SL: Sleep latency
SRT: Sleep restriction therapy
TIB: Time in bed
TRS: Treatment-resistant schizophrenia
TST: Total sleep time
UCS: Unit for Complex Schizophrenia
WASO: Wake after sleep onset
WHO-5: WHO Well-being Index
